## Methods

The following paragraphs outlines the methods of the MOVEOUT study in accordance with the SPIRIT (Standard Protocol Items: Recommendations for Interventional Trials) guidelines [52]. Recruitment, data collection, and intervention training was commenced prior to publication of the protocol (but after registration to ClinicalTrials), and parts of the sections pertaining to past events are therefore written in past tense below.

The MOVEOUT study is a cluster-randomised trial with randomisation occurring at school level. Elementary schools with one or more classes enrolled was randomly assigned to the intervention or control groups. The intervention consisted of a two-day training course on EOtC given to schoolteachers followed by the teachers applying EOtC for at least five hours a week with their class, in 1–2 weekly sessions for one school year. The training course was supplemented by two one-hour inspirational webinars during the first half of the school year (see TIDieR checklist for more detailed description [49]). The schools assigned to the control group will continue their teaching as usual for one school year upon which they will also receive the intervention. See timeline of enrolment, allocation, intervention, and data collection according to SPIRIT in Table 1 and Fig. 3.

**Table 1 Tab1:** Participant timeline according to SPIRIT

	STUDY PERIOD							
					Implementation			
	Enrolment	Pre-test A	Pre-test B	Allocation		Post-test A	Post-test B	Close-out
Time point	-18 mo.	-2 mo.	-1 mo.	0 mo.	4 mo.	10 mo.	11 mo.	14 mo.
**ENROLMENT**	x							
Eligibility screen	x							
Informed consent	x							
Allocation (cluster)				x				

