### Intervention

The intervention is based on the TEACHOUT intervention [49]. It is comprised of a two-day training course (13 h in total) on EOtC for teachers who afterwards implement EOtC in 1–2 weekly sessions, a total of at least five hours per week, for one schoolyear (in this study, August 2022 to June 2023, Month 4 to 14, see Fig. 4). The EOtC sessions in the schools are delivered by one or more of the teachers across different school subjects in various places and settings outside the school buildings.

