#### Statistical analyses

Estimation of intervention effects (H1, H2, and H3 of Sub-study 1) will be computed using a ‘per-protocol’ analysis [67]. All classes in the intervention group not adhering to the classification of ‘regular EOtC’ (an average of > 150 min of weekly EOtC over the school year) and all classes in control group practicing too high amount of EOtC (average of > 150 min of weekly EOtC over the school year) will be excluded. These analyses will be complemented with sensitivity analyses, following the principle of ‘intention-to-treat’ [67] which will include all schools in the analyses irrespective of their adherence to the intervention or control condition.

Linear mixed models (LMM) will be used to analyse how post-test scores varies as a function of whether the pupils were assigned to the intervention or the control group while taking into account pre-test scores, sex, age, and random effects of classes and schools. Please, see the H1 and H2 pre-registration for further information on the pre-processing steps and statistical modelling used for these data [51]. The base model used to assess H3 (effects on school motivation, wellbeing, and academic achievement) will include baseline as a covariate and school and class ID as random factor, and group allocation as the fixed effect of primary interest. Follow-up stepwise modelling will be used to investigate the contribution of previously shown confounders, i.e. primarily the number of weekly EOtC sessions [26], age, and sex [23, 68, 69], to the base models. All sub-studies will be reported following the CONSORT statements and flowchart [70].

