#### Statistical analyses

PA intensities during EOtC and usual school sessions will be analysed in three LMM’s with sessions as unit of analysis to investigate each PA intensity (i.e., MVPA, LPA, and sedentary time) as a function of whether the pupils have taken part of a EOtC or usual school session (H4). The base model will include school days, nested in observations nested in pupils, nested in school class as random factors, and EOtC/usual sessions as the fixed effect.

Differences in pedagogical and didactical practice will be analysed in six LMM’s (H5, one for each of the elements) with sessions as unit of analyses to investigate pedagogical and didactical practice as a function of the degree to which the practice occurred during a EOtC or usual session. The base model will include school days, nested in school class as random factor, and EOtC/usual sessions as the fixed effect. With school days as unit of analysis, two LMM’s (H5) will be used to analyse how school motivation and learning environment perceptions vary as a function of whether the pupils have taken part of a EOtC or usual school days. The base model will include observations in pupils, nested in school classes as random factors, and EOtC/usual school day as the fixed effect.

Follow-up stepwise modelling will be used to investigate if previously shown confounders, i.e., length of EOtC sessions [26], age, and gender [23, 68, 69], will improve the PA intensity, school motivation, and learning environment perception base models.

The mechanisms of EOtC (H6) will be analysed in individual secondary structural equation models (SEM) for each of the three proximal outcomes, i.e., session PA, school motivation, and learning environment perception. In all three models, EOtC/usual schooldays or session will be included and the types of EOtC pedagogy applied in the session or schooldays will be investigated as mediators [80].

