### Evaluation of implementation

#### Design

Adherence to the intervention will be investigated in a repeated design with weekly monitoring of EOtC practised during the intervention in the intervention group and control group (Month 4 to Month 14, see Table 1). Quality of delivery, variations, facilitating and limiting contextual factors at school, local, and municipality level, and teachers’ acceptability of the intervention will be investigated through semi structured interviews [81] with intervention group teachers taking place in the second half of the implementation period (Month 10, see Table 1).

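### Weekly EOtC sessions are the delivered dose, not a confounder, so the follow-up models that add them no longer estimate the effect of allocation

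*Protocol article*

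**What the plan says.** The relevant text is in the Protocol article, Sub-study 1, Statistical analyses.

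- The general linear mixed model relates post-test scores to assigned group, "taking into account pre-test scores, sex, age, and random effects of classes and schools". For H1 and H2 the reader is sent to a pre-registration that is not shown.
- The H3 base model has the baseline score as covariate, school and class as random factors, and "group allocation as the fixed effect of primary interest".
- The next sentence reads "Follow-up stepwise modelling will be used to investigate the contribution of previously shown confounders", and specifies which: "previously shown confounders, i.e. primarily the number of weekly EOtC sessions", followed by age and sex.

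Elsewhere the article says what those sessions are. Under Intervention, trained teachers "implement EOtC in 1–2 weekly sessions, a total of at least five hours per week". The Methods overview describes the intervention as the course "followed by the teachers applying EOtC for at least five hours a week with their class". Under Evaluation of implementation, adherence is tracked by "weekly monitoring of EOtC practised during the intervention in the intervention group and control group".

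**The concern.** A confounder of the group effect must influence which group a school is in, or share a cause with it. Schools were randomised, and the sessions took place afterwards because of the group they were put in. The number of sessions is therefore a measure of what was delivered, and by the trial's own theory it is the route to any benefit. Conditioning on it changes the question from what assignment to EOtC does to what assignment does apart from the number of sessions held. It also lets in bias from anything at class level, such as teacher commitment, that affects both sessions and outcome.

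The stake is interpretation. Readers commonly trust a result described as adjusted for confounders more than the unadjusted one. A real benefit could then be reported as having disappeared on adjustment, or a distorted figure could be taken as the better estimate.

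**Working it through.** **1. Causal position of the variable.** Randomisation was on 1 April 2022, and EOtC was to be implemented from August 2022 to June 2023 (Randomisation; Intervention). Sessions come after allocation and cannot influence it. The source cited for the confounder label is listed in the Background among the results of TEACHOUT, which the article describes as quasi-experimental. In a non-randomised comparison the label may be defensible, but it does not carry over to a randomised one.

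**2. The plan's own figure.** Inputs from Sample size and Recruitment: 30 schools, 1.8 classes per school, 17 analysable pupils per class (867/51), intraclass correlations 0.035 (school) and 0.046 (class), one-tailed 0.05, power 95%.

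SE = √[4 × (0.035/30 + 0.046/54 + 0.919/918)] = √(4 × 0.003020) = 0.1099

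Detectable effect = (1.701 + 1.701) × 0.1099 = 0.374, with limits 0.374 ± 1.701 × 0.1099 = 0.187 to 0.561. This reproduces the article. With the 51 classes of the analytical sample, SE = 0.1119 and the detectable effect is 0.381.

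**3. What conditioning does.** Write outcome = δ·group + b·sessions + error, and let Δ be the difference in mean sessions between arms. The effect of allocation is δ + bΔ. A model that also contains sessions returns δ alone.

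**4. Size.** Class means were simulated 4,000 times per scenario (30 schools, 51 classes, the correlations above) and fitted by generalised least squares with known variances and a one-sided 0.05 test. The total effect was set to 0.374. The session distributions and the share acting through sessions are assumptions. *Separated* means uniform 1–2 sessions per week in the intervention arm and 0–0.8 in control (Δ = 1.1). *Overlapping* means 0.5–2 and 0–1.2 (Δ = 0.65).

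| Share through sessions | Distribution | Group effect without sessions (power) | With sessions (power) | SE ratio |
|---|---|---|---|---|
| All | separated | 0.374 (94%) | 0.005 (5%) | 2.155 |
| All | overlapping | 0.374 (92%) | 0.001 (5%) | 1.254 |
| Half | separated | 0.373 (94%) | 0.185 (18%) | 2.153 |
| Half | overlapping | 0.372 (94%) | 0.184 (34%) | 1.255 |
| None | separated | 0.377 (95%) | 0.376 (44%) | 2.151 |
| All, plus class factor raising sessions and outcome | separated | 0.368 (91%) | −0.213 (0.4%) | 1.754 |
| All, plus class factor raising sessions, lowering outcome | separated | 0.366 (93%) | +0.202 (24%) | 1.753 |

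The class factor is standard normal, adds 0.25 sessions per SD and shifts the outcome by 0.1 SD up or down. Arm and sessions correlate at about 0.64 (overlapping) to 0.91 (separated, without the class factor).

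**5. Hand checks.**
- No mediation, separated: 0.374/(2.151 × 0.1119) = 1.55; 1.55 − 1.70 = −0.15, which gives power of about 44%. With the overlapping ratio, 0.374/(1.255 × 0.1119) = 2.66; 2.66 − 1.70 = 0.96, or about 83%. The 44% therefore belongs to well-separated arms.
- Class factor: the within-arm variance of sessions is 1/12 + 0.25² = 0.146 in the intervention arm and 0.8²/12 + 0.25² = 0.116 in control, mean 0.131. The spurious slope is 0.1 × 0.25/0.131 = 0.191 per session, and 0.191 × 1.1 = 0.21, close to the simulated shifts.

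**The case against.** The best reply is that sessions enter only a follow-up step. The model named for assessing H3 does not contain them, and nothing says the follow-up model replaces it. Looking at dose is also sensible: the Discussion expects that control teachers may use EOtC anyway and regards the weekly monitoring data as important for the analysis. All of this stands. It limits the problem to the follow-up models, but it does not make the confounder label right or tell a reader how to take the group coefficient from those models.

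Several stronger readings are tempting, and the article does not support them:

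- **That the main effect estimates are contaminated.** The H3 base model has no sessions term. Nor does the model listed for H1 and H2, and their pre-registration is not available to check.
- **That sessions are the randomised exposure itself.** Schools were randomised to a group; sessions are what was then delivered.
- **That adjustment always drives the effect toward zero.** It does so only as far as the effect runs through session count. Otherwise the harm is lost precision, or bias in either direction.
- **That the stepwise p-values are invalid.** The article does not say how terms are selected, and its wording also fits a planned comparison of nested models.
- **That session length distorts Sub-study 2.** Its text, "Follow-up stepwise modelling will be used to investigate if previously shown confounders", does make length a follow-up term. Whether activity time is scaled to session length, and how long usual sessions last, are not given.

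**Conclusion.** The point holds in limited form. The number of weekly EOtC sessions is wrongly called a confounder of a randomised group effect. In any follow-up model that includes it, the group coefficient is not the effect of the intervention. The primary H3 estimate is sound as long as it is taken from the base model.

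On the assumptions shown, an effect of 0.374 becomes about 0.00, about 0.185 or about 0.376 when all, half or none of it acts through sessions. It becomes −0.21 or +0.20 when, under full mediation, an unmeasured class factor also drives sessions. The standard error is 1.25 to 2.2 times larger. These figures illustrate and do not forecast: the article gives no session distribution and no mediated share. The exclusion of classes by weekly EOtC minutes in the per-protocol analysis was not simulated. It should separate the arms further and so raise the collinearity.

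A smaller inconsistency sits beside this one. The general model fixes sex and age in advance, while the H3 description two sentences later leaves them to the follow-up step.

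**What to change.** - Stop describing weekly EOtC sessions as a confounder, and remove them from every model used to estimate or interpret the group effect.
- State that the H3 effect is taken from the base model, with baseline score, age and sex fixed in advance, as the general model in the same section already does for sex and age.
- Report weekly sessions only in a separately labelled dose-response or mediation analysis. Say there that session counts were not randomised and that the group coefficient is not the intervention effect.

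The cost is wording only. No new data are needed and the weekly monitoring keeps its use. The change should be recorded before the final analyses.

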### Sub-study 2: mechanisms of EOtC

#### Design

We will investigate the mechanisms of EOtC in a within-subjects design. Pupils in the intervention group will have their PA intensities measured during two randomly chosen EOtC and two usual school days in the first half of the implementation period (Month 4 to 7, see Table 1). The pupils will answer a school motivation and learning environment questionnaire at the end of each day. The pedagogical and didactical elements will be observed during sessions.

#### Outcome measures

*PA intensities* will be measured with wrist mounted Axivity® AX3 accelerometers during school sessions and data will be processed as in Sub-study 1.

*Motivation for the teaching activities* will be measured at pupil-level with the Interest/Enjoyment (3-items), Perceived Choice/autonomy (3-items), and Perceived Competence (3-items) sub-scales of the Intrinsic Motivation Inventory (IMI) [71]. The IMI is an activity-specific measure for intrinsic motivation and basic needs satisfaction [36, 72] specially designed to be distributed immediately after an activity. Experiences of Relatedness was measured with three items inspired by the relatedness satisfaction subscales of the Basic Psychological Need Satisfaction Scales, Basic Psychological Need Satisfaction and Frustration Scale (BPNSNF) [73] and Psychological Need States in Sport-Scale (PNSS-S) [74].

*Learning environment perception* will be measured at pupil level with the Learning Rating Scale (LRS) [75]. LRS is a 4-item scale answered on a 10 cm visual analogue scale and assesses the pupils’ perceptions of how much they learn at school, how well they are getting along, and how well the teaching methods fit them.

*Pedagogical and didactical elements* will be quantified with an adapted version of the elementary school teaching practice observation scheme, Einblicknahme in die Lehr- und Lernsituation [76], using items 1–35 of the Danish version [77]. The observation scheme includes five pedagogical and didactical themes including class management; recognition and motivation; structure and consolidation; autonomy and participation; and differentiation. The scheme will be supplemented by six EOtC-specific [32, 35] and two lesson movement integration items [78, 79], as well as measures of what type of place the teaching takes place outside the school buildings [39]. These eight items will be used as a sixth theme to measure action-centred, experiential, inquiry-based, play-based learning processes theorised to pertain in particular to EOtC.

#### Statistical analyses

PA intensities during EOtC and usual school sessions will be analysed in three LMM’s with sessions as unit of analysis to investigate each PA intensity (i.e., MVPA, LPA, and sedentary time) as a function of whether the pupils have taken part of a EOtC or usual school session (H4). The base model will include school days, nested in observations nested in pupils, nested in school class as random factors, and EOtC/usual sessions as the fixed effect.

Differences in pedagogical and didactical practice will be analysed in six LMM’s (H5, one for each of the elements) with sessions as unit of analyses to investigate pedagogical and didactical practice as a function of the degree to which the practice occurred during a EOtC or usual session. The base model will include school days, nested in school class as random factor, and EOtC/usual sessions as the fixed effect. With school days as unit of analysis, two LMM’s (H5) will be used to analyse how school motivation and learning environment perceptions vary as a function of whether the pupils have taken part of a EOtC or usual school days. The base model will include observations in pupils, nested in school classes as random factors, and EOtC/usual school day as the fixed effect.

Follow-up stepwise modelling will be used to investigate if previously shown confounders, i.e., length of EOtC sessions [26], age, and gender [23, 68, 69], will improve the PA intensity, school motivation, and learning environment perception base models.

The mechanisms of EOtC (H6) will be analysed in individual secondary structural equation models (SEM) for each of the three proximal outcomes, i.e., session PA, school motivation, and learning environment perception. In all three models, EOtC/usual schooldays or session will be included and the types of EOtC pedagogy applied in the session or schooldays will be investigated as mediators [80].

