**Fig. 2 Fig2:**
[figure not shown]
Illustrations of the hypotheses of the two sub-studies

#### Sub-study 1

Effects of EOtC (see full pre-registered protocol for H1 and H2 ([51]).

H1 Pupils in the intervention group will retain higher PA intensities compared to the control group, specifically a) more MVPA, b) more LPA, and c) less SED time (referred to in the following only as PA intensities).H2 Pupils in the intervention group will retain a) more running, b) more walking, c) more standing, and d) less sitting time compared to the control group.H3 Pupils in the intervention group will achieve higher school motivation, wellbeing, and academic achievement compared to the control group.

#### Sub-study 2

Mechanisms of EOtC. The unit of analysis is schooldays or sessions.

H4 EOtC schooldays or sessions will be associated with higher PA intensities, higher levels of intrinsic motivation, and more positive perceptions of the teaching environment compared to usual schooldays or sessions.H5 The pedagogical and didactical elements during EOtC sessions will be different from the pedagogical and didactical elements during usual sessions.H6 The expected association between EOtC and PA intensities, intrinsic motivation, and perceptions of the teaching environment will be mediated by the pedagogical and didactical elements of the EOtC sessions.

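### The five pupil-level mechanism models have no day or session effect shared by classmates, so standard errors for EOtC versus usual teaching are too small whenever such an effect exists (should-fix)

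*Protocol article*

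**What the plan says.** All references are to the protocol article, Sub-study 2: mechanisms of EOtC, unless stated otherwise.

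- **Design.** Each intervention-group pupil is "measured during two randomly chosen EOtC and two usual school days".
- **PA intensities (three models, sessions as unit).** "The base model will include school days, nested in observations nested in pupils, nested in school class as random factors".
- **School motivation and learning environment (two models, school days as unit).** "The base model will include observations in pupils, nested in school classes as random factors, and EOtC/usual school day as the fixed effect".
- **Pedagogical and didactical elements (six models).** "The base model will include school days, nested in school class as random factor, and EOtC/usual sessions as the fixed effect".
- **Mediation (H6).** Structural equation models in which "EOtC/usual schooldays or session will be included and the types of EOtC pedagogy applied in the session or schooldays will be investigated as mediators". No clustering structure is described.

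Statistical analyses labels the motivation and learning-environment models H5. Their content is that of H4 under Sub-studies and hypotheses: "EOtC schooldays or sessions will be associated with higher PA intensities, higher levels of intrinsic motivation, and more positive perceptions of the teaching environment". They are treated here as H4 models.

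**The concern.** The introductory part of Methods describes teachers applying EOtC with their class. On a measured day or in a measured session, all pupils of a class therefore have the same exposure. They also share the lesson, the teacher, the place and the weather. Whatever these add to a pupil's activity or motivation on that occasion is common to the whole class, and it lies at the level where EOtC and usual teaching are compared.

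Pupil and class intercepts do not deal with this. They largely cancel from a contrast made within pupils and within classes. A day effect nested inside a pupil is private to that pupil, so the PA models as written treat classmates' deviations on the same day as independent. The questionnaire models have no day term at all. If classmates do share a day or session effect, each pupil is counted as a separate replicate of something that happened once per class. Intervals for H4 would then be too narrow and the 5% level would not hold.

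A shared effect is plausible on the plan's own theory. H6 supposes that pedagogy, observed by session, drives pupils' activity, motivation and perceptions. The Discussion also gives weather as a reason for repeating the PA measurements.

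**Working it through.** **1. The plan's own figure.** No power or precision figure is given for Sub-study 2. The only calculation is for Sub-study 1 (Sample size): d = 0.374 [0.187, 0.561], 95% power, one-tailed. It reproduces with 30 schools, 1.8 classes per school, 17 pupils per class, ICCs of 0.035 (school) and 0.046 (class), and 28 degrees of freedom:

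(1.701 + 1.701) x sqrt{4 [0.035/30 + 0.046/54 + 0.919/918]} = 0.374, interval [0.187, 0.561].

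This does not bear on the mechanism models, but it confirms 17 pupils per class as the planned analysed number.

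**2. Inputs.**
- Pupils per class: n = 21 - 4 = 17 (Recruitment and participants; Sample size). This is Sub-study 1's attrition allowance, used here as an assumption.
- Classes: 51 expected, allocated 1:1, so C is about 26 in the intervention group.
- Days per class: two EOtC and two usual (Design).
- Significance level: 0.05 (Data processing); tests taken as two-sided here.
- rho, the class-day share of the day-to-day variance within pupils: not given in the document, so a range is shown.

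**3. Formula, one value per pupil-day.** Let s2_cd be the variance of the effect shared by a class on a day and s2_e the pupil's own day-to-day variance. Each class contributes the mean of two EOtC days minus the mean of two usual days.

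- Correct variance of the contrast: (s2_cd + s2_e/n)/C
- Variance reported when days sit inside pupils or are omitted: (s2_cd + s2_e)/(C n)
- Ratio: 1 + (n - 1) rho, with rho = s2_cd/(s2_cd + s2_e)

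At n = 17 the true standard error is sqrt(1 + 16 rho) times the reported one. The real error rate of the nominal 5% test is 2[1 - Phi(1.96/sqrt(1 + 16 rho))].

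**4. Results.** The simulation used 26 classes, 17 pupils, 4 days, no EOtC effect and 4,000 runs.

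| rho | Variance ratio | True/reported SE | Type I error, formula | Type I error, simulated | Simulated, class-day as error stratum |
|---|---|---|---|---|---|
| 0 | 1.00 | 1.00 | 5.0% | 4.7% | 4.5% |
| 0.01 | 1.16 | 1.08 | 6.9% | 7.1% | 5.2% |
| 0.05 | 1.80 | 1.34 | 14.4% | 14.7% | 5.2% |
| 0.10 | 2.60 | 1.61 | 22.4% | 21.5% | 5.1% |
| 0.20 | 4.20 | 2.05 | 33.9% | 33.2% | 4.7% |

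With no pupil losses (n = 21) the SE ratios at rho 0.05, 0.10 and 0.20 are 1.41, 1.73 and 2.24.

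**5. Session-level check.** One simulated data set had two sessions per day, EOtC status constant within the day, and class-day variance equal to 10% of the day-within-pupil variance of the two-session means. Fitting the literal nesting gave SE 0.048. Adding a class-day component gave 0.081, a ratio of 1.69. A single data set is only an illustration, but it agrees with the 1.61 in the table.

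**The case against.** Several points on the other side are sound.

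- **The size is not known.** The document gives no class-day correlation. At rho 0.01 the standard error is understated by a factor of only 1.08, and at zero there is no error. A reader might infer that the standard errors are far too small. That states the upper end of an assumed range as fact.
- **The table fits the questionnaire models best.** The PA models use sessions as the unit. If a measured EOtC day also holds usual sessions, which the document does not rule out, exposure varies within the day. The missing shared level then includes the class-session, and the class-day formula is only a guide.
- **The PA wording may be a slip.** Days nested in observations nested in pupils is inverted as written, so the intended model is uncertain. Even so, no reading of the sentence yields a day effect common to classmates, and the questionnaire models have no day term under any reading.
- **The pedagogy models are not a contradiction.** A reader might take their day-within-class term as proof that the plan is inconsistent with itself. Their outcome is observed by session and has no pupil level, so a different random structure is to be expected.
- **H6 is not shown to be wrong.** A reader might extend the point to the mediation paths. The article names structural equation models without giving their clustering. A multilevel or cluster-robust version would fit the text, and a condensed article may leave that detail to the full plan. Only a single-level model on pupil rows would repeat each class-session mediator once per pupil.
- **The check has a limit.** The simulated 4.5-5.2% comes from a class-day-level analysis, not from a fitted crossed model. It also does not cover an EOtC effect that differs between classes.

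What none of this answers is that the random effects of the pupil-level H4 models are stated, they omit the shared day or session term, and nothing elsewhere supplies it. The stepwise covariates (session length, age, gender) do not replace it.

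**Conclusion.** The point holds for the five pupil-level models that test H4: three for PA intensity, one for motivation and one for learning environment. Followed as written, they understate the standard error of the EOtC-versus-usual contrast whenever classmates share a day or session effect. The understatement runs from negligible to about twofold for rho from 0 to 0.20. This rests on 17 pupils per class, one value per pupil-day and a balanced design of four days per class.

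The randomised comparisons H1-H3 and the six pedagogy models are unaffected, and no error is established for H6. Because the defect lies outside the efficacy question and its size is unknown, it is a should-fix.

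**What to change.** In all pupil-level H4 models, add a random effect for school day within class, crossed with pupils within class. In the session-level PA models, also add session within class-day. Use Satterthwaite or Kenward-Roger degrees of freedom, since the effective replicates are about 26 x 4 = 104 class-days, not pupil-days. Restate the PA nesting in the right order, and label the motivation and learning-environment models H4. For H6, state a matching multilevel or cluster-robust structure, with EOtC and pedagogy at class-session level and outcomes at pupil level.

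The cost is a change of model wording. Days and sessions are already the stated units of analysis, so no new measurement should be needed, although the document does not say explicitly that the identifiers are stored. The downside is wider intervals for the mechanism contrasts. Reporting the estimated class-day variance would show how much the term mattered.
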